#### Eligibility

The study takes place at two centers: the Department of Gastroenterology and Hepatology in the AMC of the University of Amsterdam and the Department of Gastroenterology and Hepatology in the Tjongerschans ziekenhuis, Heerenveen, The Netherlands - beginning December 2015 to January 2018. Eligible patients for participation in this clinical trial are those planned to undergo elective ERCP under deep propofol sedation, aged above 18 years, and American Society of Anesthesiologists (ASA) classification I–III, who give written informed consent.

#### Exclusion criteria

Patients are excluded if the following criteria in the patients’ medical history are applicable:Age range < 18 yearsASA classification IV or VAllergic reaction to planned medicationHistory of unregulated or malignant hypertensionSignificant ischemic heart diseaseHistory of psychological problems or psychiatric diseaseUse of drugs that affect the central nervous systemSubstance abuseChronic painPregnancySeizure disordersIncreased intracranial pressure

The schedule of enrollment, intervention, and assessment is reported according to the SPIRIT statement (Fig. 1).

**Fig. 1 Fig1:**
[figure not shown]
Schedule of enrollment, intervention, and assessment according to the Standard Protocol Items: Recommendations for Interventional Trials (SPIRIT) statement

The number of excluded patients and the reasons for their exclusion will be reported according to the SPIRIT statement.

#### Consent

Patients’ medical history and their current state of health are screened on paper during standard anesthetic pre-assessment before the scheduled sedation. The investigator uses the anesthetic pre-assessment form to screen patients for inclusion and exclusion criteria. Patients meeting inclusion criteria are contacted by phone to verify criteria and asked for their willingness to participate in this study. Further information is sent by mail if they agree to participate. Final inclusion occurs after written informed consent is provided on the day of the procedure.

If patients decline to take part in the study, they are sedated according to the AMC standards with propofol and alfentanil. The investigator or physician performing the examination can decide to withdraw a subject from the study for urgent medical reasons (allergic reactions or acute health problems).

### Randomization

Patients are randomized online in both centers after signing informed consent using the ALEA software program provided by the Clinical Research Unit (CRU) of the AMC for centralized randomization in clinical trials. Patients are allocated to a treatment arm after the anesthetic nurse has entered patient details and absence of exclusion criteria in the ALEA program.

The study is performed as a single-blinded study. Because of safety reasons the anesthetic nurse is not be blinded to the treatment arm and will therefore perform the randomization in the ALEA program. The patient, endoscopist, and investigator are blinded to the allocated treatment arm.

Patient data are collected on case report forms (CRFs) in each center. Data processing will take place in the AMC using the Castor database and will be performed by the investigator or study coordinator. The CRU also will independently monitor both locations of this multicenter trial (AMC and Tjongerschans ziekenhuis) three times using duplicated measurements documented in the hospital data management systems with complete access to all databases.

### Intervention

All patients are fasted at least 6 hours before ERCP. Antibiotic prophylaxis is given according to hospital standards. As a standard procedure, diclofenac 100 mg is administered rectally immediately before the procedure to reduce post ERCP pancreatitis [6]. Procedural sedation is performed by anesthesia nurses trained in the standards of care for procedural sedation and analgesia (PSA) according to the Dutch national guidelines. An anesthesiologist is available for liaison, supervision and emergency help. Insufflation of the duodenum during ERCP is with CO_2_ instead of air, to reduce peri-procedural pain and abdominal distension.

Patients are asked to complete a questionnaire before the procedure to assess baseline pain, drowsiness, nausea, perception, and mood using a visual analog scale (VAS) (0 = 100). Baseline assessments of the Modified Observer’s Assessment of Alertness/Sedation Scale (MOAA/S), the Aldrete recovery score and measurements of heart rate (HR), non-invasive blood pressure (NIBP), respiratory rate (RR), and oxygen saturation (SpO_2_) are recorded.

After placement of an intravenous line, an infusion of 500 ml NaCl 0.9% is started at the rate of 250 ml/h. Five minutes before insertion of the endoscope, glycopyrrolate 0.2 mg, and lidocaine 50 mg are administered intravenously. Then patients are asked to place themselves into the prone or semi-prone position. From the start of sedation till the end of the endoscopic procedure, 2 L/min of oxygen are administered by nasal cannula, and HR, SpO_2_, RR, electrocardiogram (ECG), NIBP, end-tidal carbon dioxide (etCO_2_) and sedation level measured by the MOAAS/S are collected at 5-minute intervals. An independent, blinded observer collects research data.

Both groups are sedated by a propofol TCI system (Propofol 1% MCT Fresenius). TCI means a weight pre-programmed system using the Marsh pharmacokinetic model to attain a specific estimated propofol plasma target level [7]. We start propofol TCI in both groups with a targeted plasma level of 1.5 μg/ml. Reaching this plasma level, group K is treated with esketamine (Ketanest S, Pfizer) 150 μg/kg and group A is treated with alfentanil (Rapifen, Janssen-Cilag) 2.0 μg/kg. After 2 min propofol TCI is stepped up - if needed - to a maximum targeted plasma level of 2.5 μg/ml.

Before starting the endoscopic procedure, patients are assessed for their level of sedation using the MOAA/S scale yielding at a score <2. The modified form of the MOAA/S scale uses not only the responsiveness component of the original scale (awake (5) - unresponsive (1)) but is extended with assessment of painful stimuli. As reaction to painful stimuli are still possible at anesthetic levels that block reactions to verbal commands, prodding, or shaking they can be used to assess deeper sedation levels.

If MOAA/S is > 2, e.g. the patient is too responsive to tolerate the procedure; additional sedation is provided with TCI increments of 0.5 μg/ml plasma target level. These very small steps are performed in order to avoid deep sedation. For every step up of propofol TCI, additional esketamine 50 μg/kg or alfentanil 1 μg/kg is added. Maximum dosage is 500 μg/kg ketamine or 7.5 μg/kg alfentanil.

Total dosage of propofol, alfentanil, and esketamine and the time of the total procedure and length of time between the end of the procedure (removing the scope) till reaching an MOAAS score > 4 and the declaration that the patient is ready for transport to the recovery unit, is noted.

At arrival in the recovery room, monitoring is limited to SpO_2_, RR, ECG, and NIBP only. Recovery from anesthesia and the return of psychotomotoric fitness is assessed using the modified Aldrete score at arrival and 15, 30, 45, and 60 min later. This score describes the patient’s motoric activity, mechanical respiratory function, oxygen saturation, blood pressure, and consciousness and is designed to assess patient recovery after sedation. The total score is 10 [8]. During the time in the recovery room patients have to complete the identical questionnaire they completed at baseline, on pain, drowsiness, nausea, perception, and mood, using a VAS (0 = 100). Following daily standards, post-procedural pain is indicated as VAS > 40 and is treated with 2 mg morphine intravenously; nausea indicated by a VAS > 40 will be treated with 4 mg ondansetron intravenously.

Patients have to stay for at least 1 h in the recovery room. “Ready for discharge” is declared when an Aldrete score ≥ 9 or similar to the pre-procedural score is reached. The patient must be wide awake without suffering from side effects (e.g. nausea, dizziness), with stable hemodynamic signs, and able to ambulate without assistance. A follow-up telephone call will take place on the next day after the procedure.

### Primary objective

#### Definition of primary endpoint

The primary endpoint of the study - reflecting the effectiveness of coadministration of propofol and esketamine - is the total dose of propofol used.

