**Methods/design:**

The study will be performed as a randomized controlled multicenter trial. Patients undergoing ERCP, ≥ 18 years old, with American Society of Anesthesiologists (ASA) classification I–III will be randomized after written informed consent to group K (propofol/esketamine) or to group A (propofol/alfentanil). The primary outcome, reflecting effectiveness of sedation, is the total dose of propofol. Secondary outcome parameters are patients’ and endoscopists’ satisfaction with the procedure and the number of sedation-related pulmonary and cardiovascular events. Data on sedation-related events are collected by recording of oxygen saturation (SpO_2_), respiratory rate (RR), end-tidal CO_2_ (etCO_2_), heart rate (HR), arrhythmias (electrocardiogram (ECG)), and non-invasive blood pressure (NIBP) measurements. Satisfaction parameters are collected by means of questionnaires before and after the procedure and on the following day.

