### Participants

#### Number of patients needed

Alfentanil reduces the required hypnotic dose of propofol by 20–50% at fairly low doses according to the literature [5]. A 15% reduction in propofol requirement when using esketamine instead of alfentanil would reflect a total dose reduction of propofol by up to 65%, which is not only a statistically significant but also a clinically relevant difference.

The sample size calculation is based on retrospectively obtained observational data from previous ERCPs, collected in our hospital sedation database. The primary endpoint is the difference in the dose of propofol used. The mean dosage of propofol during ERCP was 580 mg, with a standard deviation of 190 mg. We will need to study 76 subjects in each group, given power of 0.80 and type I error of 0.05, to reduce propofol requirement by about 15%. Considering a dropout rate of 10%, the estimated sample size will be 83 patients per group, thus a total of 166 patients will be randomized.

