### Secondary objectives

#### Definition of secondary endpoints

Secondary endpoints focus on the satisfaction of patients and endoscopists with sedation and side effects, and on hemodynamic stability and safety, which is reflected in the number of respiratory and cardiovascular events.

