### Statistical analysis

Statistical analyses will be performed using SPSS statistics. All data will be checked for normal distribution using the Kolmogorov test. For normally distributed data, continuous variables will be analyzed using the independent Student’s *t* test and the variables will be presented as mean ± standard deviation (SD). Non-normally distributed data will be compared using the Mann-Whitney *U* test where appropriate, and data will be presented as the median and interquartile range (IQR). For categorical variables, cross-tabulation and the Pearson chi-squared test will be applied and variables will be allegorized as number and/or percentage of the total. To compare the continuous measurements of HR, NIPD, and SpO_2_ between the groups, the area under the curve (AUC) for each value will be calculated over the different measurement time points during the procedure. A *p* value <0.05 will be considered statistically significant. Confidence intervals will be reported where appropriate.

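### Lower total propofol is read as effective sedation, but the recorded intra-procedural depth that would support that reading is not a named endpoint

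*Protocol article*

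**What the plan says.** The primary endpoint section gives the endpoint as "reflecting the effectiveness of coadministration of propofol and esketamine - is the total dose of propofol used". The abstract makes the same link: "The primary outcome, reflecting effectiveness of sedation, is the total dose of propofol". Neither sets a condition on the depth of sedation reached.

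Depth is measured. Under Intervention, "sedation level measured by the MOAAS/S are collected at 5-minute intervals", and a blinded independent observer collects the research data. The same section has both arms titrated on MOAA/S: a score below 2 is sought before the endoscopy starts, and a score above 2 leads to a propofol step-up.

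The endpoint definitions do not take this series up: "Secondary endpoints focus on the satisfaction of patients and endoscopists with sedation and side effects, and on hemodynamic stability and safety". The Statistical analysis section names a within-procedure method for three vital signs only: "To compare the continuous measurements of HR, NIPD, and SpO_2_ between the groups, the area under the curve (AUC) for each value will be calculated". Sedation does appear in the secondary assessment, but as questionnaire items. Patients report a sedation level before and after the procedure, and endoscopists give an estimate of sedation afterwards.

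On masking, the Randomization section says that patient, endoscopist and investigator are blinded and that the anesthetic nurse is not.

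**The concern.** Dose used and dose required are different quantities. They coincide when every patient is brought to, and held at, the same level. The sample size section speaks of propofol requirement, while the endpoint is the amount given. A lower amount can mean that esketamine spares propofol better than alfentanil, or that the esketamine arm was held at a lighter level.

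The common titration rule is meant to exclude the second explanation. But a titration rule states an intention, and it is carried out by a staff group in which the nurse knows the arm. The 5-minute MOAA/S series is the evidence that could show whether titration gave comparable depth, and the article assigns it no role in the comparison. At stake is the wording of the main conclusion: a significant result could be reported as more effective sedation without evidence that sedation was equally deep.

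**Working it through.** **Inputs from the sample size section.** The planning mean and SD are given as follows: "The mean dosage of propofol during ERCP was 580 mg, with a standard deviation of 190 mg". The target reduction is stated as roughly 15%, with power 0.80, type I error 0.05 and 76 patients per group. The target difference is 0.15 × 580 = 87 mg.

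**Reproducing the plan's figure.** For a two-sided comparison of two means:

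n per group = 2 × (1.96 + 0.84)² × 190² / 87² ≈ 75 by the normal approximation. The t-based solution is 75.84, so 76. A one-sided test gives 59 to 60, which does not fit. The stated 76 is therefore a two-sided figure and is correct. The sample size is not at fault.

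**Smallest significant fall at 76 per group.**

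- Standard error of the difference = 190 × √(2/76) = 30.8 mg
- Smallest significant difference = 1.96 × 30.8 ≈ 60 mg
- As a share of the mean = 60.4 / 580 = 10.4%

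**If lighter sedation were the only cause.** Assume no true sparing, an SD of 190 mg in both arms, 76 analysed per group, and x% less propofol in the esketamine arm solely because it is kept lighter. The chance of a significant result is Φ(x × 580 / 30.8 − 1.96).

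| Less propofol through lighter sedation (assumed) | Difference | Chance of significance |
|---|---|---|
| 5% | 29 mg | 0.15 |
| 10% | 58 mg | 0.47 |
| 15% | 87 mg | 0.81 |
| 20% | 116 mg | 0.96 |

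The 15% row equals the design power of 0.806. The test sees only the dose difference, so a given difference has the same chance of significance whatever its cause. The article does not say how likely any row is.

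**What the plan offers to separate the two causes.**

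- Titration: the same scale in both arms, applied by staff among whom the nurse is unblinded.
- MOAA/S series: recorded every 5 minutes during the procedure, but not a named endpoint and not in the stated within-procedure comparisons.
- Patient questionnaire: before and after the procedure, so not a measure of depth during it.
- Endoscopist questionnaire: a blinded but subjective overall estimate, given afterwards.

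**Is the target depth itself fixed?** Not fully. The Intervention section seeks a score below 2 to proceed but steps up only above 2, so a score of exactly 2 falls under neither rule. It also gives avoidance of deep sedation as the reason for small steps, while the Aim and Eligibility sections describe deep sedation as the planned technique. These statements must be reconciled before depth can serve as a measure of comparability.

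**The case against.** The strongest reply is that both arms are titrated to one scale, so the dose given is by design a measure of requirement. The stated hypothesis also asks for a lower dose with patient and endoscopist satisfaction maintained and fewer side effects, and blinded endoscopists rate sedation and ease of performance. Under-sedation would therefore have places to show. Naming three vital signs for the AUC method does not forbid an analysis of MOAA/S, and the limitations paragraph already concedes that adverse events would probably have been a more appropriate primary outcome.

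Much of this stands. The titration rule makes a large systematic difference in depth less likely, and depth is not absent from the secondary assessment. But the rule's success is assumed, not shown, and the remaining measures are subjective and taken outside the procedure. The limitations paragraph concerns a different weakness. The link from dose to effectiveness is also the article's own statement, not a detail left to an unseen analysis plan.

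A reader might go further and infer three things that the document does not support.

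- *Any fall in propofol would count as success.* It would not: significance needs about 60 mg.
- *Depth enters no endpoint at all.* Subjective sedation ratings are in the secondary assessment.
- *Aborted or failed sedation would be scored as success because it yields a low dose.* A patient who reaches the dose limits has first had propofol step-ups, so the total need not be small. For stopped procedures, simulation gives a sense of scale. Assume no true sparing and failures in the esketamine arm only, each stopped at 25% to 50% of the dose. A 5% failure share gives a chance of 0.06 to 0.10 of a significant result favouring esketamine, against 0.026 with no failures. Reaching a 15% mean fall needs an excess of 0.15/0.75 = 20% to 0.15/0.50 = 30%. The article gives no failure rates, and the handling of aborted cases is commonly left to the full protocol or analysis plan, which is not at hand.

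**Conclusion.** The point holds for depth of sedation. The article interprets a lower total dose as effectiveness without requiring or checking comparable depth, although it collects the data to do so. The planned effect of 87 mg could in principle arise from lighter sedation alone, and the primary test could not show the difference. A 10% or 15% dose reduction from that cause would be significant with probability of about 0.47 or 0.81.

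Those probabilities rest on the plan's mean and SD, equal SDs, 76 analysed per group, and the assumption that lighter sedation is the whole explanation. They show what the test cannot distinguish; they do not predict that it will happen. The endpoint and the sample size can stay. This is a worthwhile improvement in how the result may be interpreted, not an error that invalidates the trial.

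**What to change.** 1. Keep total propofol as the primary endpoint.
2. Name intra-procedural depth by arm, summarised per patient from the 5-minute MOAA/S values, as a secondary endpoint. Report the between-arm difference with its confidence interval, since a non-significant p value would not show comparability.
3. State in advance that a propofol reduction will be called greater effectiveness only if depth was not lighter in the lower-dose arm. Otherwise it is reported as a difference in dose used.
4. Before defining the depth measure, reconcile the MOAA/S criteria for proceeding and for stepping up, and the statements on whether deep sedation is intended or avoided. Which of them applies is for the clinical team to settle.

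The cost is protocol or analysis plan wording and one extra analysis. No new data and no larger sample are needed. The downside is small: a positive dose result could lose the label of effectiveness if depth differs between the arms.

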#### Assessment of primary endpoint

We will record the total amount of propofol, esketamine, alfentanil, and all other drugs administered.

### Secondary objectives

#### Definition of secondary endpoints

Secondary endpoints focus on the satisfaction of patients and endoscopists with sedation and side effects, and on hemodynamic stability and safety, which is reflected in the number of respiratory and cardiovascular events.

#### Assessment of secondary endpoint

Pain, sedation level, and side effects such as nausea and psychotomimetic effects are recorded on questionnaires that patients have to fill in before and after the procedure. To assess post-procedural satisfaction patients are contacted the day after the procedure by telephone. In addition, endoscopists’ experiences with sedation are recorded on a questionnaire after the procedure.

#### Questionnaires

Before ERCP, after the procedure and arrival on the recovery unit, and on the following day patients are asked to complete questions on pain levels, drowsiness, nausea, perception, and mood using VAS scales (0 = 100). Pain intensity will be assessed by using a 100-mm VAS scale, with 0 = no pain and 100 = worst possible pain. Nausea will be measured by a VAS scale, with 0 = none and 100 = vomiting. Perceptual change will be assessed in five categories (i.e., body, surroundings, time, reality, colors, and sounds) by using a VAS scale anchored by “normal” at one end and “extremely” at the other end. Mood states are ranked between 0 and 100 in five categories: anxious/composed, hostile/agreeable, depressed/elated, tired/energetic, and confused/clearheaded) (modified from Mortero et al. [9]).

The day after the procedure patients are contacted by telephone to assess post-procedural satisfaction. The patient is asked the same questions from part one and two of the patient questionnaire. Patients are also be interviewed about their total satisfaction with the procedure, about their physical activity level using a 5-point rating scale: 1 = chair bound; 2 = minimal (i.e. can go to the bathroom); 3 = moderate (i.e. can go around the house and garden); 4 = almost normal; and 5 = normal, and they are asked if they would recommend this sedation regime to one of their friends. Endoscopists have to fill in questionnaires on their estimation of pain, sedation, ease of performance, and satisfaction with the procedure.

Pulmonary and cardiovascular vital signs are electronically recorded throughout the procedure and include SpO_2_ measured by pulse oximetry, etCO_2_, RR, HR, arrhythmias, and NIBP. Sedation-related pulmonary and cardiovascular incidents are defined according to the International Sedation Task Force of the World Society of Intravenous Anaesthesia (SIVA) consensus statement for standardized definitions and terminology for sedation-related adverse events [10]. Pulmonary incidents are defined as oxygen desaturation (SpO_2_ 75–90%) for < 60 s, severe (SpO_2_ < 75% at any time) or prolonged (SpO_2_ < 90% for >60 s) oxygen desaturation, apnea, prolonged apnea (>60 s), airway obstruction with need for airway interventions: facemask ventilation, guedel, nasopharyngeal airway, and endotracheal tube. Cardiovascular incidents are defined as bradycardia*, tachycardia*, hypotension*, hypertension* (*as a change >25% from baseline and/or necessitating an intervention), cardiovascular collapse and arrest. In addition, the use of atropine, ephedrine or phenylephrine intravenously to treat hypotension or bradycardia is noted.

